### Interim analyses {21b}

No formal interim analysis was planned. The monitors will be responsible for recommending that the investigators update the trial design or stop the trial early on the basis of clear evidence of harm or effectiveness before the plan is completed.

### Methods for population and missing data analysis {20c}

A per-protocol analysis is planned focused on subjects who regularly took the treatment drugs every day or nearly every day. Missing values will be imputed with the last available data or the mean value for that group.

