#### Criteria for discontinuing or modifying allocated intervention {11b}

Possible reasons for withdrawal include (but not limited to) the following: subject’s voluntary withdrawal; the doctor will withdraw the subject according to clinical indications; subjects were lost to follow-up. Other conditions that may lead to treatment suspension will be evaluated and determined by investigators. If the protocol or ICF needs to be amended, the researchers are required to submit the amendment to the ethics committee for approval. Approved protocols or ICF amendments will be available to researchers prior to implementation. If an overdose occurs during the study period, the investigator should immediately notify the study leader and the principal investigator within 24 h but no later than the second day.

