### Outcomes {12}

The primary efficacy outcome is the level of serum hs-CRP at 6 months. The secondary outcomes include imaging examination (the maximal diameter of AAA, the maximal thickness of mural thrombus, and the length of aneurysm), major adverse cardiovascular and cerebrovascular events (MACCE, including AAA transformation, non-fatal myocardial infarction, acute congestive heart failure, stent thrombosis, ischemia-driven target vessel revascularization, vascular amputation, stroke, cardiovascular death, and all-cause death), other laboratory tests (troponin T, interleukin 6, D-dimer, and coagulation function). Blood will be taken at entry and 1 and 6 months to assess changes in circulatory indexes. CTA will be performed at entry and 6 months, depending on local ethics guidelines. The safety outcomes include bleeding events defined according to the Bleeding Academic Research Consortium criteria (BARC), liver function (determined by alanine aminotransferase), and renal function (determined based on the creatinine clearance rate). Detailed endpoints are listed in Additional file 1: Appendix A, and detailed definitions of endpoints are shown in Additional file 1: Appendix B. The results of the BANBOO trial will be interpreted based on all endpoints.

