### Sample size calculation {14}

Power calculations are based on a superiority comparison of the primary endpoint. Assuming the level of serum hs-CRP in the aspirin arm (control) is 4.79 ± 3.2 mg/L at 6 months, and taking the drop-out rate is 10%, 30 patients in each arm (60 in total) are planned to be enrolled and randomly assigned in a 1:1 ratio, to provide 90% power to detect a 2.54 mg/L absolute value reduction in rivaroxaban arm (intervention) in comparison with that in aspirin group with a 2-sided type I error of 0.05.

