## Statistical considerations

### Statistical methods for primary and secondary outcomes {20a}

The primary endpoint analysis will be performed according to the intention-to-treat principle. The main aim of this study is to investigate whether rivaroxaban is superior to aspirin in reducing the level of serum hs-CRP in patients with AAA and hs-CRP elevation at 6 months. The null hypothesis (H0) for this analysis is that the level of the primary endpoint in the intervention arm is the same as that of the control arm, namely P0 = P1. The alternative hypothesis (H1) is that the levels of the primary endpoint in the two arms is not equal, namely P0 ≠ P1, and the superiority test is conducted at the 2-sided significance level of 0.05.

Continuous variables are presented as the mean ± standard deviation or the median with interquartile range and compared between two arms via *T*-test or Mann–Whitney *U* test. Categorical variables are presented as counts and percentages and compared between two arms via *χ*^2^ test. Kaplan–Meier curves and Log-rank tests are used to describe the cumulative incidences of MACCE and bleeding events. The differences in the risk of AAA between the two arms are estimated using a Cox proportional hazards model. A two-sided *P* < 0.05 is considered to be statistically significant. All statistical analyses are performed using the SAS (Version 9.3) software.

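### Filling missing 6-month hs-CRP with the last value or the group mean is unsound on either reading: the arm mean gives a 7.8% type I error at the planned drop-out, and a carried value is not the 6-month outcome

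*Protocol article*

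**What the plan says.** The missing-data rule in the protocol article is one sentence, in Methods for population and missing data analysis {20c}: "Missing values will be imputed with the last available data or the mean value for that group". It sets no order between the two options, is not limited to secondary outcomes, and names no missing-data assumption.

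The rule reaches the primary test. Outcomes {12} states: "The primary efficacy outcome is the level of serum hs-CRP at 6 months". Statistical methods {20a} adds: "The primary endpoint analysis will be performed according to the intention-to-treat principle". Continuous variables are "compared between two arms via *T*-test or Mann–Whitney *U* test", and "the superiority test is conducted at the 2-sided significance level of 0.05". Sample size calculation {14} expects 10% drop-out from 30 patients per arm. Table 1 and Implementation {16c} show hs-CRP measured at entry, 1 month and 6 months only, and Table 2 requires an entry value of at least 2 mg/L.

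**The concern.** The two halves of the rule fail in different ways.

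- **Arm mean.** A value filled with the mean of its own arm carries no information. The test nevertheless counts it as an observation, and it adds nothing to the within-arm spread. The standard error is too small and the P value too low.
- **Last value.** A value carried forward is the 1-month result, about five months old, or the baseline result on which the patient was selected. Neither is the 6-month level that the endpoint names.

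At stake are the stated 5% level of the primary test under the first option and the meaning of the estimated difference under the second. Because no order is fixed, the text also leaves open which analysis is the primary one.

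**Working it through.** **Inputs from the documents.** Sample size calculation {14}: 30 per arm; drop-out 10%, so 0.10 × 30 = 3 per arm; control mean 4.79 and SD 3.2 mg/L; difference 2.54 mg/L. Statistical methods {20a}: two-sided 0.05.

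**Assumptions, not in the documents.** Between-visit correlation 0.5, log-normal shape where stated, baseline and 1-month means, and unequal drop-out splits. Simulations used 40,000 trials per scenario (8,000 for Mann–Whitney).

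**The plan's own figure.** The stated level is 5%. Without imputation, a t-test on 27 versus 27 observed values has a simulated size of 4.9%, so random drop-out alone does not break the test. The stated 30 per arm does not follow from its own inputs: 2 × (1.960 + 1.282)² × 3.2² / 2.54² = 33.4, so 34 evaluable, and 34/0.9 gives 38 per arm. That is a separate point, and the size calculation below does not use it.

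**Option 1: own-arm mean.** Let o be the number observed per arm and SS the pooled within-arm sum of squares.

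- Correct SE: √[SS/(2o−2) × 2/o]
- SE after imputation: √[SS/58 × 2/30], because filled values add nothing to SS but count towards n
- Ratio: √[((2o−2)/58) × (o/30)]
- True size: 2 × P(t with 2o−2 df > 2.002 × ratio), where 2.002 is the two-sided 5% point of t with 58 df

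For 3 missing per arm: √[(52/58) × (27/30)] = √0.807 = 0.898, and 2.002 × 0.898 = 1.80.

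| Missing per arm | SE ratio | True two-sided size |
|---|---|---|
| 1 | 0.966 | 5.8% |
| 2 | 0.932 | 6.8% |
| 3 (planned) | 0.898 | 7.8% |
| 5 | 0.830 | 10.3% |
| 6 | 0.797 | 11.8% |

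This assumes normal data and completely random drop-out, under which the difference itself stays unbiased. Simulation at 3 missing gives 7.7% (normal) and 7.5% (log-normal). Mann–Whitney does not help: 8.5% with 3 and 16.1% with 6 missing per arm (log-normal).

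**Option 2: last value carried forward.**

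- *No effect, 3 missing in each arm:* simulated size 4.7% to 5.1%. There is no inflation.
- *Real effect, baseline carried, equal baselines:* 2.54 × 27/30 = 2.29 mg/L. Simulated power is 77%, against 82% on observed values.
- *Real effect, 1-month value carried* (assumed rivaroxaban 1-month mean 3.5 against 4.79): 0.9 × 2.54 + 0.1 × 1.29 = 2.42 mg/L.
- *No effect, unequal drop-out, baseline carried* (assumed common fall of 2 mg/L): for 5 versus 1 drop-outs, 2 × (5/30 − 1/30) = 0.27 mg/L spurious difference, size 5.8%. For 6 versus 0, 2 × 6/30 = 0.40 mg/L, size 7.3%. The arm with more drop-outs looks worse.

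**The open choice.** Taking the more favourable of the two imputations, with the t-test fixed and 3 missing per arm, gives a simulated size of 8.1% to 8.5%.

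**The case against.** The best defence reads the rule as a sequence: the last value if there is one, otherwise the mean. Every randomised patient has a baseline hs-CRP because it is an entry criterion, so the mean would never be used for the primary endpoint and the 7.8% would not arise. The text allows this reading, and a fuller protocol or analysis plan may fix the order. It answers the type I error but not the substitution: a baseline or 1-month value would still be analysed as the 6-month outcome. Under equal drop-out the resulting dilution is conservative, and the bias illustration rests on assumed inputs. Both limits stand.

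It can also be said that Blinding {17a} keeps the statistical researchers unaware of allocation. That protects against favouring one arm. It does not settle which imputation is primary, since a two-sided P value can be compared across methods under coded labels. Whether anyone would choose that way is not something the document shows.

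Three stronger readings are tempting and are not supported:

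- *That the rule as a whole both biases the comparison and inflates the error rate.* Under completely random drop-out with matching trajectories, the mean inflates without bias and the carried value keeps its size.
- *That the imputation choice yields an 11% error rate.* About 11% appears in simulation only when the analyst may also choose between the t-test and Mann–Whitney. Most of the excess over 8% therefore comes from the open choice of test in Statistical methods {20a}.
- *That stopping treatment means leaving the study.* Section {11b} says "the doctor will withdraw the subject according to clinical indications" among possible reasons for withdrawal and mentions treatment suspension separately. It does not say that outcome collection ends when the drug is stopped.

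Finally, a t-test on observed values already holds its size, so deletion alone cures the inflation. That is true under completely random drop-out. A repeated-measures model relies on the weaker assumption that drop-out is random given the observed values.

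**Conclusion.** The point stands, in conditional form. The rule is wrong as written because neither option gives a sound primary analysis of 6-month hs-CRP.

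- If the arm mean is used, the SE is about 10% too small and the true two-sided type I error is 7.8% at the planned drop-out. This follows from the protocol's own sample size, level and drop-out, and it already assumes completely random missingness. It takes the word group to mean treatment arm; an overall mean would instead dilute the difference.
- If the last value is carried forward, size is near 5% under equal drop-out. The estimate is diluted when the effect builds up over time, and it is biased when drop-out or trajectories differ by arm. The size of that bias (0.27 mg/L in the 5 versus 1 illustration, about 11% of the 2.54 mg/L design difference) depends on assumed inputs.
- If the choice stays open, the error rate is about 8% with the t-test.

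**What to change.** Delete both single imputations for the primary endpoint. Analyse the observed hs-CRP by a likelihood-based repeated-measures model using the baseline, 1-month and 6-month values, with the 6-month contrast between arms as the primary result. Multiple imputation from the baseline and 1-month values is an acceptable alternative. Add one pre-specified sensitivity analysis for data not missing at random, such as a shift applied to imputed values.

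If hs-CRP is analysed on the log scale, state that the effect becomes a ratio, and also report the mg/L difference, because that is what Sample size calculation {14} powers.

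The cost is a change of wording, a little programming and a slightly wider confidence interval. No new data are needed. Error rates and power under the replacement model were not computed here. Part of the apparent power is lost: in simulation, mean imputation raised it from 82% to 87% at 3 missing per arm, but that gain was only the understated standard error.

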## Oversite and monitoring {21a}

During the trial, the trial monitor will monitor the trial in accordance with the pre-specified monitoring plan. The trial monitor will review the accuracy and completeness of the study data at appropriate times and ensure compliance with the clinical study protocol. The study monitor may request all documents from the investigator as well as required records, including the medical records (office, clinic, or hospital) of the subjects in this study. Original documentation must be provided to confirm proper informed consent procedures, adherence to protocol procedures, proper reporting and follow-up of adverse events, the accuracy of data collected on case report forms, and study drug information.

## Adverse events or harms {22}

All adverse events (AEs) related to cardio-cerebrovascular, bleeding, liver, and renal damage were collected from the time subjects signed informed consent to the end of the study. The doctor should adopt the best treatment immediately after discovery and report to the ethics committee within 2 days of the occurrence. Based on study-eligible criteria, pregnant or would-be pregnant women are excluded from the study population. If unplanned pregnancy occurs during the study period, all pregnancies should be reported to the study leader and principal investigator; pregnant women should immediately discontinue research drugs and drop out of the study.

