### Objectives {7}

The primary objective is to explore the anti-inflammatory efficacy of rivaroxaban in the treatment of AAA with hs-CRP elevation and to investigate the application value of rivaroxaban for AAA. The secondary objectives are to analyze the safety of rivaroxaban for AAA and the efficacy of rivaroxaban on antithrombosis and alleviating inflammatory lesions.

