## Methods: participants, interventions, and outcomes

### Study setting {9}

Initial baseline assessment includes contact information, physical examination, vital signs, demographical data, previous history, clinical characteristics, admission diagnosis, imaging examination, and laboratory test data. Once a standardized interview is performed, the data will be recorded in each subject’s case report form (CRF). Follow-up visits will occur at entry, 1 month, and 6 months after treatment initiation, and outcome data will be collected. Detailed collecting information on visits is listed in Table 1. An imaging subgroup is set up to analyze the effect of rivaroxaban on AAA morphology. All subjects screened, regardless of whether they are eligible for randomization, are provided with follow-up calls twice at 1 month and 6 months. Any interruption of treatments due to personal reasons is required to report within 24 h. Treatment should be discontinued immediately for emergent situations, including trauma or urgent invasive procedures, for the benefit of subjects.

**Table 1 Tab1:** Collecting information on visits

Follow-up	Baseline (visit 1)	1 month (visit 2, ± 7 days)	6 months (visit 3, ± 7 days)
Inclusion/exclusion criteria	X		
Physical examination	X		
Vital signs	X		
ICF	X		
Contact information	X		
Demographic data	X		
Previous history	X		
Admitting diagnosis	X		
Subject guidance	X		
Drug therapy	X	X	X
hs-CRP	X	X	X
Imaging examination	X		X
MACCE		X	X
Other laboratory tests	X	X	X
Bleeding events (BARC)	X	X	X
Liver function	X	X	X
Renal function	X	X	X
Subject compliance		X	X

*ICF* inform consent form, *hs-CRP* high-sensitivity C-reactive protein, *MACCE* major adverse cardiovascular and cerebrovascular event, *BARC* Bleeding Academic Research Consortium

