### Inclusion and exclusion criteria {10}

The BANBOO study is designed to enroll 60 AAA subjects with hs-CRP elevation. Subjects aged 18 to 85 years, 30–50 mm in diameter of the aneurysm, and serum hs-CRP ≥ 2 mg/L are eligible for enrollment. Each enrolled subject should provide written informed consent before randomization. Complete inclusion and exclusion criteria are listed in Table 2 and Table 3.

**Table 2 Tab2:** Inclusion criteria

Inclusion criteria
1. 18–85 years old
2. AAA diagnosed by CTA; the maximal diameter of aneurysm is 30–50 mm
3. Serum hs-CRP ≥ 2 mg/L
4. Written informed consent

*AAA* abdominal aortic aneurysm, *CTA* computed tomography angioplasty, *hs-CRP* high-sensitivity C-reactive protein

**Table 3 Tab3:** Exclusion criteria

Exclusion criteria
1. ACS (unstable angina and acute myocardial infarction)
2. Dual antiplatelet therapy for stable CHD less than 6 months after PCI or ACS less than 1 year after PCI
3. Acute congestive heart failure or left ventricular ejection fraction ≤ 40%
4. Suffered from infectious diseases within 2 months before screening and infection has not been controlled more than 1 month
5. Active hepatitis, the elevation of alanine aminotransferase (ALT) value > 5 × the upper limit of normal
6. Severe renal failure (CrCl < 30 ml/min)
7. Life expectancy is less than 1 year
8. Any situation may interfere with the research process, such as dementia, paralysis, alcoholism, etc
9. Pregnancy or women during the lactation period
10. Suffered from hereditary connective tissue disease, such as Marfan’s syndrome, etc
11. Known allergies or intolerance to aspirin or rivaroxaban
12. AAA tends to rupture or has ruptured, and abdominal pain aggravates
13. Major surgery within 1 month
14. Active stage of severe peptic ulcer or previous bleeding events (including retinal or vitreous hemorrhage, urinary tract hemorrhage, etc.) within 6 months
15. Have participated in other ongoing clinical studies
16. Refuse to provide a written informed consent
17. Other unsuitable conditions adjudicated by investigators

*ACS* acute coronary syndrome, *CHD* coronary heart disease, *PCI* percutaneous coronary intervention, *CrCl* creatinine clearance rate, CrCl = body weight(kg) × (140-age)/[0.818 × CREA(μmol/L)][serum creatinine (CREA) is tested by enzymatic method. Female: above data results × 0.85]

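### Adverse-event collection is limited to four classes, which is narrower than the trial's general safety objective and leaves no stated place to record intercurrent infection that could raise hs-CRP

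*Protocol article*

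**What the plan says.** Adverse events or harms {22} fixes the scope of collection: "All adverse events (AEs) related to cardio-cerebrovascular, bleeding, liver, and renal damage were collected", from consent to the end of the study. The same section then requires a report to the ethics committee within 2 days.

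Outcomes {12} names the safety outcomes: "The safety outcomes include bleeding events defined according to the Bleeding Academic Research Consortium criteria (BARC), liver function" (by alanine aminotransferase) and renal function (by creatinine clearance). Table 1 in Study setting {9} has rows for MACCE, BARC bleeding, liver function and renal function. It has no row for other adverse events, serious adverse events or infection.

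Objectives {7} is wider: "The secondary objectives are to analyze the safety of rivaroxaban for AAA", with no restriction by organ class. The Discussion presents the trial as the first in this population to assess both efficacy and safety against aspirin, and notes that no clinical study of the drug in this field has yet been reported.

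For efficacy, Outcomes {12} states: "The primary efficacy outcome is the level of serum hs-CRP at 6 months". Infection is mentioned as a screening exclusion, number 4 in Table 3: "Suffered from infectious diseases within 2 months before screening and infection has not been controlled more than 1 month".

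**The concern.** The scope of adverse-event collection is a rule the article states, not a detail it leaves to a fuller document. Followed exactly, it has two consequences.

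- **Safety.** A non-fatal harm outside the four classes, even a serious one, would not be collected as an adverse event. The ethics-reporting duty follows directly on that definition, so such an event has no stated route to the committee. Interim analyses {21b} lets the monitors recommend stopping for clear harm, but the stated event data would cover only the four classes. In a trial described as the first in its population, collection limited to expected classes cannot reveal an unexpected harm, yet the result would be read as the safety of rivaroxaban in AAA.
- **Efficacy.** The primary endpoint is an inflammatory marker read at one visit. The protocol screens out recent infection at entry, then gives no stated place to record infection over the following six months. If infections are not recorded, values affected by them cannot be set aside or examined in a sensitivity analysis.

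**Working it through.** The plan gives no figure on this point, so the main check is a comparison of sections.

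**Step 1. Scope of collection against scope of the objective**

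| Place | Scope |
|---|---|
| Objectives {7} | Safety in general |
| Adverse events or harms {22} | Cardio-cerebrovascular, bleeding, liver, renal |
| Outcomes {12}, safety | BARC bleeding, liver function, renal function |
| Table 1, Study setting {9} | MACCE, BARC bleeding, liver function, renal function |

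The three operational places agree with each other. The mismatch is between them and the objective.

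**Step 2. What is captured outside the four classes**

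- Death from any cause, because MACCE ends with "vascular amputation, stroke, cardiovascular death, and all-cause death" (Outcomes {12}).
- Pregnancy (Adverse events or harms {22}).
- Overdose (Criteria for discontinuing {11b}).
- Treatment interruption for personal reasons must be reported within 24 h (Study setting {9}), but this is not an event record.

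Non-fatal events in any other organ system remain without a stated route.

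**Step 3. Infection after randomization**

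It falls outside the four classes and has no row in Table 1. Strategies to improve adherence {11c} has trial drugs recorded in the CRF, which might show an anti-infective but would not itself record the illness, its date or its severity.

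**Step 4. Illustration of what an unrecorded infection could do to the primary comparison**

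Inputs from Sample size calculation {14}: SD 3.2 mg/L, target difference 2.54 mg/L, 30 per arm, 10% drop-out, two-sided 0.05. Evaluable per arm: 30 × 0.9 = 27. The hs-CRP excess x in an infected patient is an assumption, taken over 10 to 100 mg/L.

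- Shift in an arm's mean with k infected patients: k·x/27.
- SD with one such patient in each arm: √(3.2² + p(1−p)x²), with p = 1/27. For x = 10: √(10.24 + 3.57) = 3.7.

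| Assumed x (mg/L) | Shift, one patient in one arm (mg/L) | Share of 2.54 | SD, one patient in each arm | t-test power, 27 per arm |
|---|---|---|---|---|
| 0 | 0 | 0% | 3.2 | 82% |
| 10 | 0.37 | 15% | 3.7 | 69% |
| 20 | 0.74 | 29% | 5.0 | 46% |
| 50 | 1.85 | 73% | 10.0 | 15% |
| 100 | 3.70 | 146% | 19.2 | 8% |

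The 82% in the first row is what the stated inputs give with 27 per arm. It differs from the plan's 90%, which is a separate matter and does not affect this point. The plan also allows a Mann–Whitney test, which would be less affected than the t-test shown here.

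**The case against.** The strongest defence is that the safety plan is internally coherent. The collection rule, Table 1 and the safety outcomes agree, and the objective is one general sentence that the outcomes section makes concrete. On this view the tension is only breadth of wording, and narrowing the objective would resolve it. That stands in part: narrowing is a legitimate repair where data can no longer be obtained. It does not give a non-fatal serious event outside the four classes a collection or reporting route, and no section justifies the restriction by an established safety profile in AAA.

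A second defence is that the CRF, the full protocol and the appendices are not shown, and that Oversite and monitoring {21a} gives monitors access to medical records and mentions reporting and follow-up of adverse events without naming classes. That passage concerns verification and does not widen the collection rule. The defence does carry weight for infection, where the point is an inference from the adverse-event scope and Table 1.

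Several stronger readings are tempting, and the documents do not support them:

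- That no other harm can be assessed. All-cause death, pregnancy and overdose are captured.
- That infections definitely go unrecorded. No section says so, and drug records may leave an indirect trace.
- That infection is the main cause of spurious 6-month values. Nothing in the documents ranks causes. The point needs only that infection can raise hs-CRP, which fits the protocol's description of it as an inflammatory marker and its own screening exclusion.
- That unmasked staff will classify events differently by arm. The trial is open-label and the rule needs a judgement on relatedness, but bleeding follows BARC, and liver and renal function rest on laboratory values. No section shows biased discretion.

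**Conclusion.** The point holds in a limited form. The stated scope of adverse-event collection is narrower than the stated safety objective. Outside the four classes, only all-cause death, pregnancy and overdose have a stated route, so a general statement about the safety of rivaroxaban in AAA could not be supported by the data the plan provides for. This part rests on the text alone.

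That intercurrent infection has no stated place is an inference from the same rule and Table 1. Its effect on the primary result cannot be sized from the documents. The 15% to 146% range of the target difference depends wholly on the assumed excess of 10 to 100 mg/L, on one affected patient among 27 in one arm, and on a comparison of means. It shows that a single case could matter in a trial this small, not that one will occur.

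The amendment should be made: it brings data collection into line with the trial's own objective at modest cost.

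**What to change.** 1. Amend Adverse events or harms {22} to collect all adverse events and all serious adverse events, whatever the organ system, from consent to the end of the study. Make clear that ethics reporting covers serious events in every class.
2. Keep cardio-cerebrovascular, bleeding, liver and renal events as events of special interest, and report all classes by arm.
3. Add a row to Table 1 and a CRF item recording acute infection or inflammatory illness at each hs-CRP sample (entry, 1 month, 6 months).
4. Add a prespecified sensitivity analysis of the primary endpoint for hs-CRP values affected by such illness, alongside the intention-to-treat analysis. Wider event collection alone would change no hs-CRP analysis.
5. For subjects whose follow-up is complete and whose data cannot be recovered, limit the safety objective and conclusion to the classes collected. This may apply to many: recruitment began in October 2021 with a planned duration of 18 months, and the article appeared in June 2023 describing the study as ongoing.

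The cost is modest extra data entry and coding for 60 subjects over three visits, plus an amendment that needs ethics approval.
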